### Sample

The participating students attended the 21 Victorian government secondary schools that had agreed to participate in this project. Four schools are located in metropolitan Melbourne; ten are located in metropolitan fringe and major regional areas; and seven are in regional and rural areas. The student populations of six schools are in the medium high/high range in term of socioeconomic status, as measured by the Department of Education and Early Childhood Development's (DEECD) Student Family Occupation (SFO) index. The student populations of ten schools are in the medium range. The student populations of five schools are in the low range. Written active consent was sought from the 2700 year eight students in the 21 participating schools and their parents. Of this total population 1746 or 64.7% agreed to participate in the research. Intervention students numbered 1230. Control students numbered 516.

### The drug education intervention

The student intervention material and an accompanying teacher implementation manual and teacher training program have been developed from material trialled in the pilot program [23], which in turn drew on a range of earlier Australian research and development projects in drug education and resilience education. These included the School Health and Alcohol Harm Reduction Project (SHAHRP) and GET WISE: Working on Illicits in School Drug Education [9,34]. The education program comprises 10 lesson plans in year eight and 8 in year nine that address issues around the use of alcohol, tobacco, cannabis and other illicit drugs (see Table 1). Experience from the SHAHRP study indicated that this number of lessons can provide adequate coverage and be accommodated within a secondary school curriculum. A number of tasks are designed to be undertaken at home in collaboration with a parent so as to draw out their influence on decision-making about drug use [35]. As alcohol is the most commonly used drug by Australian young people, and the drug that causes them the greatest harm, it will receive the greatest coverage, followed by tobacco and cannabis.

**Table 1 T1:** Year eight and year nine lesson plans

Lesson	Year 8	Year 9
1	WHAT IS A DRUG? - Introduction, agreements, definitions and drug categories	PRIORITIES AND CONCERNS - Identifying what young people value and worry about and what worries they have around drugs

2	ALCOHOL AND EFFECTS AND STANDARD DRINKS - How alcohol effects the body, assessing harms associated with use, pouring standard drinks, understanding blood alcohol content and safer levels of use	FACING FACTS AND FINDING SOLUTIONS - Alcohol and Cannabis- guidelines on use and the research that informs them

3	PARTY BEHAVIOURS AND ALCOHOL - The relationship between levels of alcohol use and the risk of harm to self and others	USING YOUR RESOURCES - Pouring standard drinks, matching harms to levels of alcohol use, identifying strategies to reduce harm

4	PREVALENCE AND NORMS - Dispelling myths about levels of drug use amongst young people, identifying reasons for use/non -use	WINDING UP, WINDING DOWN - Learning about the effects/risks of Amphetamine type stimulants, identifying drug-free ways of achieving 'high' and 'serene' states of mind

5	TOBACCO - Considering gender differences in relation to smoking; the impact of media messages	DRUGS, DISINHIBITION, SEXUAL VULNERABILITY AND VIOLENCE - Discussing sexual vulnerability in relation to drug use, identifying strategies for avoiding or reducing harm

6	CANNABIS - Information about cannabis and its effects, identifying risks associated with Cannabis use	INVISIBLE RISKS - Information about injecting drug use, blood-borne viruses and methods of protection

7	RISK REDUCTION - Assessing risk and developing strategies to avoid or minimise harm	PERSONAL CONFIDENCE - AND DRUG USE - Developing and rehearsing positive self talk, refusal skills and tactics for peer negotiation

8	INFLUENCES - Identifying social and media influences to use alcohol	GETTING HELP AND TALKING WITH ADULTS - Information about heroin, rehearsing steps for practical first aid in situations involving overdose, rehearsing help seeking with adults

9	OPTIONS AND DECISIONS - Generating and rehearsing strategies to reduce harms associated with drug use	

10	STANDING UP FOR YOURSELF - Providing peer support, using assertion skills in situations involving alcohol	

The education program incorporates the elements of effective practice identified by reviews of school drug education [19-22,25,36]. This literature identifies the importance of basing programs on evidence of proven effect; the needs of students; provision of essential knowledge; adequate coverage of salient issues; and use of interactive learning strategies that enhance negotiation skills, involve participants in problem-solving and engage them in deconstructing the social pressures and perceived norms around drug use. The curriculum is also informed by research in the field of resilience education that identifies social competence, problem-solving, autonomy and a sense of purpose as key attributes of resilient young people [37], and highlights the importance of participatory and developmentally appropriate learning strategies in enhancing social and emotional learning [38].

Each year all teachers delivering the classroom program will participate in an intensive two-day professional learning program that provides a grounding in the evidence-base informing the study and active sampling of each of the lesson activities they will be teaching their students. Emphasis will be given to modelling and explicit leadership coaching in use of the participatory methods.

### Student survey instrument and measurement of change

The survey instrument to measure change is a development of the self-completion questionnaire used in SHAHRP and was trialled in the pilot research that preceded this study [9,23]. Self-report is well accepted practice in studies of this type and research indicates little inconsistency between self report and other measures of drug use [39,40] The instrument will collect information on knowledge, patterns and context of use, attitudes and harms experienced in relation to alcohol, tobacco, cannabis and other illicit drug use. As was done in the pilot study, scales will be constructed to measure overall change in AOD knowledge (38 items), attitudes (4/5 items per drug type), and harms (5/10 items per drug type)

A student generated code, based on easily remembered fragments of personal information, is used to maintain confidentiality, while allowing individual matching over the course of the study. As part of the pilot research, feedback was obtained from experts in school drug education and students in the target group. This indicated the instrument had both content and face validity. The Cronbach's alpha test was used to measure the internal consistency of the AOD knowledge, attitude and harm scales generated from the pilot survey responses. The results for the pilot AOD knowledge and alcohol, tobacco, cannabis and other drugs attitude and harm scales are presented in Table 2. The internal consistency co-efficient of all indices was significant. In the case of the knowledge scale and all the harm scales the respective co-efficients were high (α = .609-.949), indicating each scale was a good measure of the intended single latent construct [41]. The attitude scale co-efficients were lower, although still significant. Factor analysis of the attitudes towards alcohol, tobacco and other drugs indicated there were two main factors in the data accounting for between 53.5% and 57.9% of the total variation in each case. One factor pertained to attitudes about knowledge and communication; the other pertained to attitudes about harm.

**Table 2 T2:** Internal consistency of knowledge, attitude and harm scales

Scale	alpha	p	Component factors	% of variance
Knowledge scale	.859	< 0.001		

Attitudes towards alcohol	.387	< 0.001	Knowledge and communication	30.6

			Harm	23.5

Alcohol harm scale	.949	< 0.001		

Attitudes towards tobacco	.445	< 0.001	Harm	32.4

			Knowledge and communication	21.1

Tobacco harm scale	.802	< 0.001		

Attitudes towards cannabis	.548	< 0.001		

Cannabis harm scale	.891	< 0.001		

Attitudes towards other drugs	.284	< 0.001	Knowledge and communication	32.7

			Harm	25.2

Other drugs harm scale	.609	< 0.001		

### Blinding

Participants cannot be blinded to intervention in this sort of psycho-social educational intervention, nor can program deliverers or outcome assessors.

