**Methods/Design:**

A cluster randomised school drug education trial will be conducted with 1746 junior high school students in 21 Victorian secondary schools over a period of three years. Both the schools and students have actively consented to participate in the study. The education program comprises ten lessons in year eight (13-14 year olds) and eight in year nine (14-15 year olds) that address issues around the use of alcohol, tobacco, cannabis and other illicit drugs. Control students will receive the drug education normally provided in their schools. Students will be tested at baseline, at the end of each intervention year and also at the end of year ten. A self completion questionnaire will be used to collect information on knowledge, patterns and context of use, attitudes and harms experienced in relation to alcohol, tobacco, cannabis and other illicit drug use. Multi-level modelling will be the method of analysis because it can best accommodate hierarchically structured data. All analyses will be conducted on an Intent-to-Treat basis. In addition, focus groups will be conducted with teachers and students in five of the 14 intervention schools, subsequent to delivery of the year eight and nine programs. This will provide qualitative data about the effectiveness of the lessons and the relevance of the materials.

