### Statistical analysis

Multi-level modelling can best accommodate hierarchically structured data and will be used in this analysis, adjusting for any baseline differences between the intervention and control groups [42,43]. The hierarchy in this longitudinal multi-level dataset comprises level 1 units (occasions of repeated measurement), nested within the level 2 units (the individual student), nested within the level 3 units (the school). Stata version 10.0 will be used for model fitting, with a three-level mixed regression model fitted to the data to account for the repeated observations [44]. If necessary, the knowledge, consumption and harm scales will be log-transformed to satisfy the assumption of normality. If normality cannot be achieved by log-transformation, non-parametric procedures will be used for analysis. All analyses will be conducted on an Intent-to-Treat basis. Complete-case analysis (CCA) will be complemented with multiple imputation analysis (MIA) to account for missing data.

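### The blinding statement is too broad: students and program teachers cannot be blinded, but nothing in the protocol prevents data entry, code linkage, scoring and transformation decisions from being made with arm withheld

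*Protocol article*

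**What the plan says.** The Blinding section is one sentence: "Participants cannot be blinded to intervention in this sort of psycho-social educational intervention, nor can program deliverers or outcome assessors". It has no qualification and lists outcome assessors separately from participants.

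The outcomes are described elsewhere. The abstract's Methods/Design paragraph says: "A self completion questionnaire will be used to collect information on knowledge, patterns and context of use, attitudes and harms experienced". The section on the student survey instrument says: "The survey instrument to measure change is a development of the self-completion questionnaire used in SHAHRP". Records are linked over the surveys by code: "A student generated code, based on easily remembered fragments of personal information, is used to maintain confidentiality, while allowing individual matching over the course". Scoring follows the pilot: "As was done in the pilot study, scales will be constructed to measure overall change in AOD knowledge (38 items", with item counts also given for the attitude and harm scales.

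The Statistical analysis section leaves some decisions until the data are seen: "If necessary, the knowledge, consumption and harm scales will be log-transformed to satisfy the assumption of normality", and then "If normality cannot be achieved by log-transformation, non-parametric procedures will be used for analysis". It also adjusts for whatever baseline differences appear between the arms. Complete-case and multiple-imputation analyses are both to be run.

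**The concern.** The sentence gives three groups as impossible to blind. For students and program teachers the reason is plain: they know whether the program is taught in their school. For anyone else who might be called an outcome assessor no reason is given, and the way outcomes are collected suggests none. A reader or a data team could take the sentence as settled and make no attempt to withhold arm from the work that follows questionnaire completion.

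What is at stake is a cheap protection. Some decisions depend on the data (whether to transform, whether to move to non-parametric methods, what to adjust for). If they are made with arm visible, nobody can later show that they were made independently of the result. This carries more weight because the study both develops and assesses the program, and because members of the research team drew the allocation themselves (Study design).

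**Working it through.** No figure in the plan depends on this point, so there is none to reproduce. The check is mainly a comparison of the text, step by step, with two small calculations.

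**1. Which steps need knowledge of arm?**

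| Step | Where described | Does it need arm? |
|---|---|---|
| Student completes questionnaire | Abstract, Methods/Design; Student survey instrument | The student knows the arm; unavoidable |
| Program teacher delivers lessons | The drug education intervention | The teacher knows the arm; unavoidable |
| Data entry | Not described; implied by a questionnaire | No |
| Linking surveys by code | Student survey instrument | No: matching is on the code |
| Scoring scales | Student survey instrument | No: follows the pilot |
| Log-transform or non-parametric | Statistical analysis | No: can be judged on pooled data |
| Adjusting for baseline differences between arms | Statistical analysis | Yes, as worded |
| Fitting the treatment comparison | Statistical analysis | Yes, but it comes last |

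The impossibility holds for the first two rows. For the next four rows the document gives no obstacle.

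**2. Can normality be judged on pooled data?** The sample size section plans for an effect of 0.15 without naming its metric. Two readings:
- Standardised mean difference, schools split 14:7. Variance between arms, in units of the within-arm variance: (14/21) × (7/21) × 0.15² = 0.2222 × 0.0225 = 0.0050. Share of the total: 0.0050/1.0050 = 0.5%.
- Cohen's f. Share of the total: 0.15²/(1 + 0.15²) = 0.0225/1.0225 = 2.2%.

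On either reading, an effect of the planned size would add little to the spread of the pooled data, so leaving arm out loses almost nothing when normality is assessed.

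**3. Would A/B labels be enough?** No. With 14 intervention and 7 control schools, and 1230 against 516 students (1230/516 = 2.38), the larger group is plainly the intervention arm. School is level 3 of the model, so a school identifier must stay in the file. It has to be a random number, with no arm variable alongside it.

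**4. Size of the risk, worst case, on assumed inputs.** Take k analyses of one contrast under no effect, with equicorrelated normal test statistics, and report the most favourable. The error rate is P(max|Z| > 1.96). Simulated values, 1,000,000 draws each:

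| k | correlation 0.7 | 0.8 | 0.9 |
|---|---|---|---|
| 3 | 11% | 10% | 8% |
| 4 | 13% | 11% | 9% |

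A second simulation used assumed data shaped like this trial: 14 v 7 schools, 83 students each, skewed counts, school log-SD 0.10 to 0.25, tests on school means. Each single analysis had about 4-5% error. Taking the smallest p-value of raw, log and rank analyses gave about 7%. Taking the smallest of six, which also included baseline-adjusted versions, gave about 11%.

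**The case against.** The strongest reply is that with self-report the student is the outcome assessor, so the sentence is true in that sense. It does not mention data staff or analysts, and silence about them is normal in an article that condenses a fuller protocol or analysis plan. Much of this stands. A reader might infer that the protocol rules out blinding of everyone who analyses the data; it does not say so. What remains is that assessors are named apart from participants under a flat statement of impossibility. That is a fault in what is stated, not an omission.

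Other stronger readings are also unsupported:
- That linkage involves judgement on near-matching codes. No matching rule is described, and no manual linkage is mentioned.
- That the program's developers will themselves score and analyse. The document does not say who will.
- That the analysis choices are wide open. The transformation rule is ordered and triggered by normality, scoring follows the pilot, and complete-case and imputed analyses are both run. An analysis plan not shown may narrow the choices further.
- That masked data handling is the only protection left. Concealed stratified randomisation and intention-to-treat analysis are both stated.
- That the trial's error rate is 8-13%. That figure assumes deliberate selection, which the plan does not propose.

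One objection bears on the remedy: adjustment for baseline differences between arms cannot be decided without arm. That is correct, so the adjustment rule must change as well.

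**Conclusion.** The concern holds in a limited form. The impossibility is correct for students and program teachers and is stated too broadly beyond them. Nothing in the document prevents data entry, code linkage, scoring and the normality decisions from being done with arm withheld. The current adjustment rule is the exception, since it requires arm.

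No stated figure changes. The error rates above (about 7-13%, depending on the model and the number of analyses) show what arm-aware selection could do at worst under assumed inputs; they are not a property of the plan. The conclusion rests on the outcomes being self-completed and code-identified as described, with no rater involved. Masking would not touch reporting bias from unblinded students, and its value depends on how well the staff concerned already know the schools. The point is worth acting on because the protection is inexpensive and the plan does contain data-dependent decisions.

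**What to change.** 1. **Blinding section.** Limit the impossibility to students and program teachers. Add that data entry, code linkage, scale scoring and the decisions on normality, transformation and non-parametric analysis will be completed and dated on files pooled over arms. These files carry a random school number and no arm variable (not A/B labels), and arm is merged only afterwards.
2. **Statistical analysis section.** Replace adjustment for observed differences between arms with covariates named in advance, for example the baseline value of each outcome and the randomisation strata.

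Cost: rewording in two sections, recoded school numbers and one dated decision log. A team member who neither scores nor analyses must hold the allocation key, which may be awkward in a small team. Staff who recognise schools will be imperfectly masked, and the report should say so.

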### Research ethics

The study was approved by Edith Cowan University's and the University of Melbourne's human research ethics committees. It was also approved by the Research Branch, Education Policy and Research Division of the Victorian Department of Education and Early Childhood Development.

### Statistical analysis

Multi-level modelling can best accommodate hierarchically structured data and will be used in this analysis, adjusting for any baseline differences between the intervention and control groups [42,43]. The hierarchy in this longitudinal multi-level dataset comprises level 1 units (occasions of repeated measurement), nested within the level 2 units (the individual student), nested within the level 3 units (the school). Stata version 10.0 will be used for model fitting, with a three-level mixed regression model fitted to the data to account for the repeated observations [44]. If necessary, the knowledge, consumption and harm scales will be log-transformed to satisfy the assumption of normality. If normality cannot be achieved by log-transformation, non-parametric procedures will be used for analysis. All analyses will be conducted on an Intent-to-Treat basis. Complete-case analysis (CCA) will be complemented with multiple imputation analysis (MIA) to account for missing data.

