The study will follow a cohort of students from the start of year eight, when most are 13 years old, to the end of year ten, when most would have turned 16. Pre intervention, baseline testing will occur at the beginning of year eight (Mar/Apr). The first phase of the drug education intervention will occur in the middle of that year (Jul/Sep). Post 1 testing will occur at the end of the same year (Nov/Dec), approximately 8 months subsequent to baseline. The second phase of the drug education intervention for the students, now in year nine, will occur in the middle of the second year of the study. Post 2 testing will occur at the end of the second year. In the third year, when the students are in year ten, no further drug education lessons will be provided as part of this study, but schools will continue with their usual year ten drug education curriculum. Post 3 testing will occur at the end of the year. Throughout the study control students will receive the drug education normally provided by their school. The research sequence is illustrated in Figure 1. Fidelity data will be collected from all participating teachers on a lesson by lesson basis via an on-line survey. In addition, focus groups/interviews will be used to collect qualitative information about the relevance and suitability of lesson materials from students and teachers in a sample of five of the 14 intervention schools following delivery of both the year eight and the year nine program. The student focus groups will be one hour in duration with a roughly even mix of six to eight males and females. Teacher interviews will also be one hour long with either individuals, or small groups of two to three respondents.

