### Sample size calculation

The ability to detect small changes in substance use, knowledge, attitudes and harms experienced is central to this study. The primary outcome is a change in alcohol consumption patterns and associated harm, and accordingly sample size estimations are based on detecting a small effect size of .15 in relation to these measures. This effect size was chosen on the basis of previous school drug education studies [9,32].

The target sample size has been estimated using G*Power v.3.1.3 software where α = 0.05 and 1-β error probability = 0.95 [33]. Assuming simple random sampling, a total sample size of 364 is required at the end of the study. However, there is a design effect due to the loss of effectiveness created by cluster sampling. The design effect for the SHAHRP study, which took into consideration the effect of clustering by school and a 15% annual rate of student attrition, was calculated to be 1.48. Using this correction, a total sample size of at least 539 is required to test the effectiveness of the intervention.

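### The stated adjustment rule ties baseline adjustment to observed arm differences; using each outcome's baseline value in every model would be more precise at almost no cost

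*Protocol article*

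**What the plan says.** The Statistical analysis section of the protocol article gives one rule for baseline adjustment: multi-level modelling "will be used in this analysis, adjusting for any baseline differences between the intervention and control groups". It names no covariate and does not say how a difference would be judged.

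The same section describes a longitudinal model, "with a three-level mixed regression model fitted to the data to account for the repeated observations", with measurement occasions as level 1, students as level 2 and schools as level 3. It does not say whether the baseline survey is one of those occasions or is kept apart as a covariate.

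A baseline survey is planned for the whole cohort. The abstract says "Students will be tested at baseline, at the end of each intervention year and also at the end of year ten", and Study design puts the first survey before any lessons: "Pre intervention, baseline testing will occur at the beginning of year eight (Mar/Apr"). The student-generated code described under the survey instrument allows individual records to be matched across surveys.

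**The concern.** In a randomised trial, baseline differences between arms arise by chance, and their observed size is a poor guide to which variables need adjusting for. A covariate earns its place by predicting the outcome. With 14 schools against 7, a strongly prognostic variable may happen to look balanced while a weak one differs noticeably. If the first is left out and the second put in, the estimate loses precision for no gain.

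Such a rule also cannot be settled until baseline data have been compared by arm. The trial has many outcomes (knowledge, plus consumption, attitudes and harms across several drug types), so the adjustment could differ from one outcome to the next. The covariate most likely to help, the baseline value of the outcome itself, is already scheduled for measurement. Whether it is used should not depend on how the arms compare.

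**Working it through.** **1. The plan's own sample size, and what it suggests about baseline.** Inputs from Sample size calculation: effect size 0.15 (metric not stated), "α = 0.05 and 1-β error probability = 0.95", and 364 before the design effect. Take a two-group repeated-measures between-groups F test with f = 0.15, m occasions and correlation ρ = 0.5 (assumed), with non-centrality λ = f²·N·m / (1 + (m − 1)ρ):
- m = 4 gives N = 364, the stated figure, and 364 × 1.48 = 538.7, rounded up to 539.
- m = 3 gives N = 388.
- A two-sided comparison of two means at d = 0.15 with equal groups gives 2312, so it does not reproduce the figure.

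Four occasions are reached only by counting baseline. This suggests, without proving, that baseline was thought of as an occasion in the model. The sample size itself does not depend on the adjustment clause.

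**2. Relative variance of three ways of handling baseline.** Let r be the correlation between baseline and follow-up (not given; range assumed). Relative to a follow-up comparison that ignores baseline (variance 1):
- baseline as a fixed covariate: 1 − r²
- baseline as an occasion with a free group-by-time term, so that the contrast is a difference in change: 2(1 − r)

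| r | fixed covariate | change contrast |
|---|---|---|
| 0.3 | 0.91 | 1.40 |
| 0.5 | 0.75 | 1.00 |
| 0.7 | 0.51 | 0.60 |

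The gap is 2(1 − r) − (1 − r²) = (1 − r)², which is positive for every r below 1.

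**3. Power.** Students remaining, if the 15% annual attrition quoted for the earlier alcohol study holds for three years: 1230 × 0.85³ = 755 and 516 × 0.85³ = 317. Mean per school: 1072 / 21 = 51.05. Design effect: 1 + 50.05 × ICC = 2.00 at an assumed ICC of 0.02. Degrees of freedom: 21 − 2 = 19. School-level and student-level correlations are assumed equal, so one variance factor applies throughout.

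SE = √[factor × 2.00 × (1/755 + 1/317)]. With factor 1, SE = 0.0947 and the non-centrality is 0.15 / 0.0947 = 1.58. Two-sided power from the non-central t:

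| r | baseline unused | change contrast | fixed adjustment |
|---|---|---|---|
| 0.3 | 0.325 | 0.25 | 0.35 |
| 0.5 | 0.325 | 0.325 | 0.41 |
| 0.7 | 0.325 | 0.49 | 0.56 |

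At ICC 0.01 and r = 0.5, power is 0.412 with baseline unused and 0.518 with fixed adjustment.

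**4. The imbalance-driven rule simulated.** The setting was 14 v 7 schools, 83 students each, ICC 0.03 (assumed), analysis of school means and 15,000 runs per setting. The rule adjusted only when the baseline arm difference had p < 0.05; that threshold is an assumption, since the article gives none.

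| r | power, always adjust | power, adjust if different | type I error, adjust if different |
|---|---|---|---|
| 0.3 | 0.33 | 0.32 | 0.049 |
| 0.5 | 0.39 | 0.32 | 0.042 |
| 0.7 | 0.54 | 0.32 | 0.035 |

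Type I error with fixed adjustment was about 0.049 throughout. In this setting the conditional rule is conservative and gives up nearly all the available gain.

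**The case against.** The strongest reply is that the clause need not describe selection. Adjusting for any baseline differences can simply mean that baseline values go into the model, so that whatever difference exists is removed. A reader might infer that covariates will be screened by baseline significance tests, or that the baseline outcome will be left out unless the arms differ. The document supports neither: it mentions no test and no threshold, and it does not say that the baseline outcome is omitted. This stands, and it limits confidence in the point.

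A second reply is that baseline is probably in the model already, as one of the level 1 occasions. The primary outcome is framed as a change, and four occasions reproduce 364. This is plausible but does not settle the matter. An unconstrained change contrast is still less precise than fixed baseline adjustment at every r below 1, though at r = 0.7 the difference is modest (0.49 v 0.56).

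Third, the size is conditional. The article gives neither r nor an ICC. If its 0.15 is Cohen's f, the matching standardised difference for equal groups is 0.30, and at ICC 0.02 and r = 0.5 the same formula gives 0.85 without baseline and 0.93 with it. Power is then much higher either way and the gain is 8 points.

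A reader might also infer inflated false positives. The simulated rule shows none (0.035 to 0.049). Free choice among models could behave differently, but nothing in the document shows that it is intended.

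Finally, a full covariate list belongs in an analysis plan that is not shown, and its absence here is no fault. The criticism is confined to the rule that the article does state.

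**Conclusion.** The point holds as a recommendation, with moderate confidence. The only adjustment rule in the article, on its natural reading, makes adjustment depend on observed arm differences, which is the wrong criterion in a randomised trial. If the intention was general baseline adjustment, the sentence does not say so clearly and still needs correcting.

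The benefit of fixing it is precision. At 0.15 SD, ICC 0.02 and the attrition and equal-correlation assumptions above, fixed adjustment adds about 3, 9 and 23 percentage points of power at r = 0.3, 0.5 and 0.7 over ignoring baseline (0.35, 0.41 and 0.56 against 0.325). Over an unconstrained change contrast it adds about 10, 9 and 7 points (against 0.25, 0.325 and 0.49). The direction holds for any r between 0 and 1; the size rests on figures that the document does not give. The stated sample size is unaffected.

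**What to change.** Replace the clause in Statistical analysis with wording such as: *Every model will use the baseline value of the outcome analysed, whatever differences are observed between arms, either as a fixed covariate or by including baseline as an occasion with arm means constrained equal at baseline. No covariate will be selected on the basis of observed baseline imbalance.*

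The text should say which of the two forms is used, which also settles whether baseline is a level 1 occasion. Any further covariates can be left to the analysis plan, provided they are fixed there in advance.

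The cost is one or two sentences. The baseline survey and the matching code are already part of the design, so no extra data collection is needed.
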